**Fig. 3 Fig3:**
[figure not shown]
Time schedule

The actual data collection will be done by a study nurse with a BSc in Nursing. Potential confusions/problems with the raw data are discussed within the respective healthcare institution and with the leader of the study. Ambiguities with the procedure of data collection are discussed with the head of project management within the research team who also keeps a research diary. The study nurse transfers the anonymised data to the project management after the third measuring cycle. Two other study nurses enter the data into SPSS and carry out data cleansing before proceeding with the data analysis. The data of the comparison group are disclosed to the project management “PID” in encrypted form by the project manager “ZULIDAD”.

Data analysis will be performed using the IBM software programme SPSS® (version 24). The socio-demographic data are analysed descriptively (frequencies, central tendencies, standard deviations) and the outcome variables as follows:Pain intensity, duration and pain-free intervals are investigated in all dementia patients of the comparison and intervention group measuring the average duration of pain events per work shift (each work shift lasts 8.25 h) and per weekday, and the average degree of pain intensity per work shift, per work day as well as the duration of pain-free intervals with multilevel and events history analyses based on the data observation intervals T0, T1, T2.For the multilevel analyses (linear mixed models) over time, two levels are considered: the dementia patient and the healthcare institution. The event history analyses use cluster-adjusted Cox regressions. Furthermore, event history analyses will focus on evaluating the influence of the two nursing professional groups (at assistant/secondary and tertiary level), the pain pharmacotherapy (number and dosage), behavioural problems (NPI) and the psychopharmacotherapy (number and dosage).

A change in the assessment of pain by the healthcare workers is checked with interrater reliability tests. By means of the interrater reliability test, a potential variation between the two nursing groups on assistant/secondary and tertiary level is monitored.

To ensure the quality of data analyses, each data analysis step is independently checked by three different people.

Monitoring will by done bya trial master file which will be saved on a password-protected server with backup.All project steps are recorded in a diary and stored in the project folder. Project members will be instructed by the principal investigator. Their quality of work will be tested at the beginning of their activity.The data of the study participants are reviewed by external study nurses for completeness and anonymity and, if necessary, the contact person in the respective retirement and nursing home is consulted. This process is designed to protect the participants by ensuring that no personalised data leaves the nursing homes before it is entered into the statistics programme. The clinical trial meets the requirements of the Swiss Law on Human Research and adheres to the statutory provisions.

The intervention trial has been approved by the ethics committees of the canton of Thurgau (K2016/02) and Zurich (01–2016) with clearance certificates and will be conducted according to Good Clinical Practice ICH Expert Working Group (1996) [48], which is based on the Declaration of Helsinki (2013) [49]. The nurse-led intervention trial complies with the following basic ethical principles of research [50, 51]: respect of persons, beneficence and justice. The authors of the intervention trial declare no conflict of interest. The process evaluation, the intervention protocol and the results of the trial will be published.

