Sustainability and veracity of the interventions are ensured by following the comprehensive evaluation process based on Dobbins [45] that consists of:assessment of the accuracy between the conducted intervention and the study protocol: 50% of the intervention protocols are tested for compliance with the study protocol based on selected pain management strategies and structured communication skills (ISBAR, SOPIER, prompt initiation of medical prescriptions, usage of non-analgesic pain management strategies) by descriptive analysis.evaluation of operating procedures that are associated with pain managementquestioning of acceptability of the interventions carried out for all health care workers with a scale from 0 (= no acceptance) to 10 (= fully accepted)compliance (adherence) of interventions for all health care workers with a scale from 0 (= no adherence) to 10 (= complete adherence)assessment of the potential for change in clinical practice among healthcare workers with a scale from 0 (= no conversion potential) to 10 (= complete transformation possible)assessment of potential change in the management of pain among health care workers with a scale from 0 (= no change in potential) to 10 (= comprehensive amendment potential)

Pain as primary outcome is measured in all people with dementia in the comparison and intervention groups by means of:pain events per shift and per week;degree of pain intensity per work shift, per week day;pain-free intervals.

Secondary outcome variables will be measured by:frequency of behavioural problems (Neuropsychiatric Inventory NPI [46]);number/dosages of psychotropic drugs;Number/dosages of analgesics.

The documentation regarding the assessment of pain by nurses is always done in duplicate, by a health care worker on different education level. Tertiary outcome variables will be measured by:changes in the assessment of pain by healthcare worker on healthcare assistant level andchanges between the two healthcare worker groups on healthcare assistant level and registered nurse level.

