Hypotheses for primary outcomes are:H_a1_: There is a 20% reduction in pain events over time before and after the intervention and between intervention and comparison groups among nursing home older people.H_a2_: There is a 50% reduction in pain intensity over time before and after the intervention and between intervention and comparison groups among older people.H_a3_: There is a 20% reduction in the duration of pain free intervals over time before and after the intervention and between intervention and comparison groups among older people.

Furthermore the following hypotheses will be explored:There is a difference in the behavioural problems score (NPI) before and after the intervention and between intervention and comparison groups among older people.There is a difference in the psychopharmacological drug numbers/dosage before and after the intervention and between intervention and comparison groups among older people.There is a difference in the numbers/dosage of painkillers before and after the intervention and between intervention and comparison groups among older people.There is a difference in pain assessment over time before and after the intervention and between intervention and comparison groups among nursing home older people.There is still a difference in pain assessment by healthcare workers on assistant level over time before and after the interventionThere is still a difference in pain assessment between healthcare workers on assistant level and registered nurses level over time before and after the intervention.

The sample size used in the trial is determined based on the requirements of event history analyses and multilevel analyses to test the mentioned hypotheses.

Event history analyses: The required number of events for a two-tailed test of individual coefficients within a Cox model with other covariates has been calculated based on the method of Hsieh and Lavori [41]. A total of *n* = 179 people and 121 events are required for a power of 0.8 and a significance level of 0.05 based on an expected hazard ratio of 0.6 (SD 0.5), a probability of occurrence of 0.75 and a drop-out rate of 10%. Both the number of people and the number of events determined in the intended study protocol can be collected.

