Multilevel analyses (linear mixed models): The required number of cases for basic evaluations using multilevel models/linear mixed models have been determined by the approximation method [47] - with equal power and significance level as in the event analyses. This approach recognises a random intercept model with covariates that only vary between older people (treatment). In order to carry out only two repeated measurements per person, approximately *n* = 47 persons are required using a regression coefficient of 1 and a standard deviation of 0.5.

There are three data monitoring cycles (T0, T1, T2) and two intervention cycles (I1, I2) to measure the primary and secondary outcomes, see Fig. 3. Each data monitoring cycle extends over 7 weeks (=49 days) and includes seven different weekdays and at least three different work shifts. The data are extracted from the older people’ specific pain diaries (degree of pain intensity), which are kept separately from conventional nursing documentation. For the description of the sample, socio-demographic data on age and gender are collected from all participants. Additional data on qualifications and professional experience are collected from nursing staff, and care needs, dementia type and severity of dementia from people with dementia.

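### Pain-free interval duration, a primary outcome, is assigned to a linear mixed model as well as to Cox regression; only Cox can handle intervals still open at day 49, and no lead analysis is named

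*Protocol article*

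**What the plan says.** All places are in the Methods of the protocol article.

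- **Outcome.** The list of primary pain measures ends with "pain-free intervals", and hypothesis H_a3 reads "There is a 20% reduction in the duration of pain free intervals over time".
- **Window.** "Each data monitoring cycle extends over 7 weeks (=49 days", and there are three such cycles (T0, T1, T2).
- **Analysis.** The data-analysis paragraph names pain intensity, pain duration and pain-free intervals, and closes the list with "as well as the duration of pain-free intervals with multilevel and events history analyses based on the data observation intervals T0, T1, T2". It continues: "For the multilevel analyses (linear mixed models) over time, two levels are considered: the dementia patient and the healthcare institution". Then: "The event history analyses use cluster-adjusted Cox regressions".
- **Sizing.** The event history calculation is for a "two-tailed test of individual coefficients within a Cox model with other covariates". It uses a hazard ratio of 0.6, a probability of occurrence of 0.75 and a drop-out rate of 10%.

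The article does not say which of the two methods leads for pain-free intervals. It also does not say how an interval still open at the end of a cycle enters the mixed model.

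**The concern.** A pain-free interval that is running when observation stops is known only to be at least as long as observed. Cox regression uses exactly that information. A standard linear mixed model needs a number. If the observed length is entered, a resident without pain for a whole cycle scores 49 days, and one who drops out pain-free on day 15 scores the same as one whose pain returned on day 15. If open intervals are dropped, the longest ones are removed preferentially.

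Either way, the more intervals lengthen, the more of them reach the limit, and the estimated change is compressed. Two analyses of one primary outcome could then disagree for a mechanical reason, with no rule for which to believe.

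**Working it through.** **Inputs**

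- Window W = 49 days (paragraph on data monitoring cycles).
- Pain events reduced by 20% (H_a1). At a constant event rate the mean interval becomes 1/0.8 = 1.25 times as long.
- Hazard ratio 0.6, SD 0.5, probability of occurrence 0.75, drop-out 10% (sample-size paragraph).
- Mean interval before the intervention, m: not given. A range is assumed.

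**The plan's own figure.** Events = (1.960 + 0.842)² / (0.25 × (ln 0.6)²) = 7.849 / (0.25 × 0.26094) = 120.3, rounded up to 121. People = 121 / 0.75 / 0.90 = 179.3, against the stated 179. Both are reproduced and neither is in dispute. The calculation itself assumes that a quarter of people have no event, so open intervals are expected.

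**Open intervals kept as complete.** Treat pain events as points in time. With N events in the window a resident has N + 1 intervals adding up to W, so the resident mean is W/(N + 1). For Poisson N with mean W/m, its expectation is m(1 − exp(−W/m)). The share of intervals cut by the cycle end is about 1/(W/m + 1).

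| m before → after (days) | Observed mean before | Observed mean after | Observed ratio (true 1.25) | Share cut before → after |
|---|---|---|---|---|
| 7 → 8.75 | 6.99 | 8.72 | 1.25 | 13% → 15% |
| 14 → 17.5 | 13.58 | 16.44 | 1.21 | 22% → 26% |
| 28 → 35 | 23.13 | 26.37 | 1.14 | 36% → 42% |
| 49 → 61.25 | 30.97 | 33.73 | 1.09 | 50% → 56% |

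**Kept against dropped.** Simulation of recurrent intervals, 6,000 residents per setting, at the planning hazard ratio of 0.6. The table gives the share of the true difference in days that survives in the resident mean.

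| m (days) | Kept as complete | Dropped |
|---|---|---|
| 5 | 98% | 99% |
| 10 | 91% | 64% |
| 20 | 58% | 24% |
| 27 | 41% | 16% |

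At 1 to 5 days, 98 to 100% survives if open intervals are kept. If single intervals are pooled instead of averaged per resident, the surviving share with open intervals kept is 89% at 2 days, 76% at 5, 63% at 10, 45% at 20 and 35% at 27.

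**Where 27 days comes from.** Assume that the 0.75 refers to one 49-day cycle, averaged over two groups with hazard ratio 0.6. Then exp(−49/27.0) = 0.163 and exp(−49/45.0) = 0.337, which average 0.25. True means of 27.0 and 45.0 days would appear, for the first interval, as 22.6 and 29.9 days. That is 7.3 of 18.0 days, or 40%.

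**Direction.** The compression works both ways. If intervals shortened by 20%, as H_a3 literally says, a mean of 28 days would fall to 22.4. The observed mean would be 22.4 × (1 − exp(−49/22.4)) = 19.89 against 23.13, a ratio of 0.86: a 14% reduction instead of 20%.

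**The case against.** **The handling of open intervals is not stated.** That is so, and an article may leave it to a fuller plan. A reader might infer that cut-off intervals will be entered as complete lengths; the text does not say this. What stands is narrower: a stated pairing of this outcome with a model that has no place for censoring, where both simple ways out lose part of the effect once intervals are long.

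**The sentence may be distributive**, with mixed models for averages and Cox for intervals. This is possible. But the method phrase directly follows the pain-free intervals, and if the distributive sense was meant, one clause settles it.

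**A censoring-aware analysis is already planned, and the trial is sized for it.** Correct. It limits the point to the parallel mixed model and the missing lead analysis.

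**Intervals may be short.** Outcomes are counted per shift and per week, which suggests a scale of days. At a mean of a week or less, the resident-level loss is negligible. The 0.75 points to longer intervals only if it refers to one cycle, which the article does not say.

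**Two stronger readings are tempting.** One is that deaths and transfers worsen the problem. The article never names them as exits; it gives only the 10% drop-out. The other is that residents who improve most lose most. The calculations give every resident the same change. Varying that common change at a baseline of 27 days does show more relative loss with larger effects (51% of the difference kept at hazard ratio 0.9, 40% at 0.6, 24% at 0.3), but that compares scenarios, not residents within a trial.

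**Conclusion.** The point holds in a limited form. On its plain reading, the plan analyses a primary time-to-event outcome with a linear mixed model alongside Cox regression and gives neither precedence. Where intervals are cut off, the mixed model is biased towards no effect. Under constant event rates, resident-level means and open intervals kept as complete, a true 25% lengthening shows as about 25%, 21%, 14% and 9% at baseline means of 7, 14, 28 and 49 days. The loss therefore runs from essentially nil to well over half, and the documents do not fix where this trial lies. No sample-size figure changes, and the planned Cox regression is not called into question by this point.

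**What to change.** In the data-analysis paragraph, name the cluster-adjusted Cox regression as the analysis of pain-free interval duration, with intervals open at day 49 or at drop-out censored. Restrict the linear mixed model to pain intensity and per-shift averages. If the distributive reading was intended, say so.

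If a multilevel analysis of pain-free time is wanted, use a summary that the window does not cut off, such as the share of observed diary shifts without pain per resident and cycle, with only shifts actually observed in the denominator.

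The cost is a change of wording and one fewer analysis of this outcome. There are three limits:

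- The shift-based share is a different quantity from interval length, and it is bounded, so a linear model for it is an approximation.
- Censoring at day 49 does not settle how intervals already running on day 1 of a cycle enter; that needs its own sentence.
- The opening paragraph of the Methods describes comparison data only from the first and 49th day and from the last RAI assessment. The shift-based summary may therefore be limited to before-after comparison within the intervention homes, and the same check is needed before between-group Cox results on intervals are promised.

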## Methods

We employ a quasi-experimental nursing-led intervention trial with a repeated measures design [36] based on a convenience sample of four nursing home clusters and a total sample of 411 dementia patients. All dementia patients in the comparison group will be obtained from the Zurich Life And Death with Advanced Dementia (ZULIDAD) Study [37]. The ZULIDAD data were collected from people with dementia (men and women), who are older than 70 years in one nursing home (*n* = 150), in 2015. Data between intervention sites and comparison site are similar because the same assessment instruments were used, based on an older person assessment instrument, and include pain duration, pain intensity, behavioural problems, differences of psychopharmacological drugs, and differences of analgesics. The comparison can be made with data from the first day and from the 49^th^ of each data collection phase (t0, t1, t2) and with a historical sample of pain duration and pain intensity from the last pain assessment documented in the older person Assessment Instrument Data (RAI) of each participant.

People with dementia in the intervention group will be are recruited in three healthcare institutions in the cantons of Thurgau and Zurich.

All healthcare workers from these three intervention institutions are included in the study, trained and coached in the provision of interventions. The following inclusion criteria apply to healthcare workers:must be at least 18 years old;must have been employed at least 12 months in the respective organisation;must work for at least 30% of a working week;be able to communicate in German.

The collection of data will take place in three nursing homes in the Canton of Thurgau and in the Canton of Zurich. For the comparison group, data from the ZULIDAD study [37] will be used.

All older people are screened for eligibility to participate in the study. Recruitment is described in Fig. 1. Only older people with documented nursing-initial-assessment symptoms of dementia are included in this intervention trial by author no. 3.

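### The stated 0.8 power does not apply to the intervention-versus-comparison contrast, because treatment varies only between homes (three against one) and both sample-size figures omit home-level variance

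*Protocol article*

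**What the plan says.** The Methods section describes a quasi-experimental trial "based on a convenience sample of four nursing home clusters and a total sample of 411 dementia patients". The comparison group consists of people "older than 70 years in one nursing home", 150 in number, observed in 2015 by the ZULIDAD study. The intervention group is recruited in three other institutions. Each of the three primary hypotheses covers both a before-after change and a difference between intervention and comparison groups.

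The sample-size paragraphs of Methods give two calculations, said to be set by what the analyses need in order to test those hypotheses. The Cox calculation is for a "two-tailed test of individual coefficients within a Cox model with other covariates", and states that "121 events are required for a power of 0.8 and a significance level of 0.05", with 179 people. Of the mixed-model calculation the article says: "This approach recognises a random intercept model with covariates that only vary between older people (treatment". It arrives at about 47 persons.

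The data-analysis paragraph of Methods names the home. For the mixed models "two levels are considered: the dementia patient and the healthcare institution", and for time-to-event outcomes "The event history analyses use cluster-adjusted Cox regressions". It does not say what the cluster unit is or how the adjustment is made.

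**The concern.** No home contributes residents to both groups, so treatment does not vary within a home. For the between-group half of each primary hypothesis, the independent units are four homes, one of them in the comparison arm. The sample sizes are instead built on independent persons. Two things are at stake. First, the stated 0.8 power is a property of a different design. Second, a difference between the ZULIDAD home and the three trial homes in case mix, practice, documentation or calendar period cannot be told apart from an intervention effect, and the data hold little information on how large such differences normally are.

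**Working it through.** **Inputs from the article (Methods).** Two-sided alpha 0.05, power 0.8, hazard ratio 0.6, SD 0.5, event probability 0.75, drop-out 10%; for the mixed model, coefficient 1, SD 0.5, two measurements per person; four homes, 411 people, 150 of them in the one comparison home.

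**Assumptions.** The 411 include the comparison group, so 411 − 150 = 261 people are in the intervention homes, taken as 87 per home. The article gives no between-home variance or intraclass correlation (ICC), so ranges are shown.

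**1. Reproducing the stated figures.**
- Cox events: (1.960 + 0.842)² / (SD² × ln(HR)²) = 7.849 / (0.25 × 0.2609) = 120.3, rounded up to 121.
- Cox people: 121 / 0.75 / 0.90 = 179.3, stated as 179.
- Mixed model: 7.849 × (1 + 1/2) / (0.25 × 1²) = 47.1, stated as about 47. This requires person and residual variances of 1 each, which the article does not state.

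An SD of 0.5 is that of a 1:1 binary covariate. The planned split is 150/411 = 0.365. Neither formula contains a home-level variance or a design effect.

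**2. Home-level test, Cox, HR 0.6, all 411 residents.** Events per person = 0.75 × 0.90 = 0.675. With home SD τ on the log hazard,

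variance = 1/(261 × 0.675) + 1/(150 × 0.675) + τ²(1/3 + 1).

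Degrees of freedom = 4 homes − 2 = 2, critical t = 4.303, and |ln 0.6| = 0.511.

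| Assumed home SD | SE | Power, 2 df |
|---|---|---|
| 0 | 0.125 | 58% |
| 0.05 | 0.137 | 52% |
| 0.1 | 0.170 | 39% |
| 0.2 | 0.262 | 21% |
| 0.3 | 0.368 | 14% |

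**3. Home-level test, linear model, coefficient 1, all 411 residents.** SE without home variance = sqrt(1.5 × (1/261 + 1/150)) = 0.125. Home variance × 4/3 is added under the root. The ICC can be based on the total variance of a single measurement (2) or of a person mean (1.5).

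| Assumed ICC | Power, base 2 | Power, base 1.5 |
|---|---|---|
| 0.01 | 70% | 76% |
| 0.02 | 53% | 60% |
| 0.05 | 30% | 37% |

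Adding residents does not cure this: at ICC 0.05 with base 2, power with unlimited residents in four homes is about 33%.

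**4. What a robust variance clustered on home would do, if that is what is meant.** In a linear model the only comparison home has residuals that sum to zero, so it adds nothing to the robust variance. In a simulated Cox model (homes of 87, 87, 87 and 150, no treatment effect, 75% events, 2000 runs), the uncorrected test of the group level difference at nominal 5% rejected 45% of the time with no home differences at all (median robust SE 0.049 against a true SD of 0.124). It rejected 45%, 50% and 49% at home SDs of 0.1, 0.2 and 0.3. For a linear outcome the rate was 44% at ICC 0 and 47–49% at ICC 0.01–0.05. A small-sample correction with 3 degrees of freedom still gave 21–26%.

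**5. Group-by-time instead of group level.** In a simulation with one measurement before and one after, and home differences constant over time, comparing change scores rejected a true null 4.6–5.1% of the time at home SDs from 0 to 0.5. A post-only comparison rejected 12% at SD 0.1 and 64% at SD 0.5. Home-by-period variation was not simulated; it would remain aliased with treatment.

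**The case against.** The strongest reply is that the plan does not ignore clustering. That stands: the institution is a level in the mixed models and the Cox models are cluster-adjusted. A reader might infer that the planned tests treat treatment as a person-level contrast; the data-analysis paragraph does not support that. The person-level treatment sits in the sample-size paragraphs. The fault in the analysis is that no adjustment can do its work with three homes against one.

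Second, a reader might take the 45% false-positive rate as a property of this plan. It is not. The article names neither the cluster unit (it could be the resident, who can have repeated pain events) nor the estimator, and the full plan may do so. The figure holds only for an uncorrected robust variance clustered on home.

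Third, a reader might infer that home fixed effects would abolish the treatment effect altogether. They remove the group level difference, but a group-by-time term stays estimable, and the hypotheses can be read that way. Whether ZULIDAD holds the repeat measures needed is not clear from the article.

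Fourth, the Cox calculation does not say which coefficient it powers, and other Cox covariates are of interest. That tempers the point for the 121 events, though the article ties both calculations to the hypotheses. Only the mixed-model text names treatment.

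Fifth, 411 far exceeds 179: 411 × 0.675 = 277 events, or 98% power without clustering. The surplus is in residents, however, and the shortage is in homes.

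Nor do the documents support a blanket statement that standard errors are several times too small. Ignoring home SDs of 0.1, 0.2 and 0.3 understates the SE by factors of about 1.4 (0.170/0.125), 2.1 (0.262/0.125) and 2.9 (0.368/0.125). Lastly, the before-after contrasts in the three intervention homes are not aliased with home, and the quasi-experimental, historical-control design is openly declared.

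**Conclusion.** The point holds for every intervention-versus-comparison contrast, which is half of each primary hypothesis. There treatment is a home-level variable with a single comparison unit, aliased also with data source and period, and the stated 0.8 power does not apply. A home-level test has power of at most about 58% for a hazard ratio of 0.6, falling to about 21% at a home SD of 0.2. For a coefficient of 1 in the linear model, power is 70–76%, 53–60% and 30–37% at ICCs of 0.01, 0.02 and 0.05. That the stated figures contain no home variance follows from the article alone, apart from the two unit variances needed to reach 47. The sizes rest on assumed home variances, equal intervention homes, and 411 including the 150. A group-by-time contrast would cancel constant home differences but not home-by-period variation.

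**What to change.** 1. In the sample-size paragraphs, state that 121 events in 179 people, and 47 people, give 0.8 power only if between-home variance is zero, and that they do not apply to the intervention-versus-comparison contrast.
2. Report the ZULIDAD contrast descriptively: estimate and interval, with the home, source and period caveat, and no confirmatory p-value. Use change from baseline or group-by-time where repeat data allow.
3. Make the within-resident change across T0, T1 and T2 in the three intervention homes the main inference. Use home as a fixed effect (a stratum in the Cox model), resident as the random effect or cluster, and cycle as a fixed effect. Show the change in each home separately, and give the expected precision of this contrast in place of the present power claim.

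The cost is an amendment to wording in the protocol and analysis plan; no new data are needed. The downside should be stated openly. The between-group claim is downgraded. The before-after result applies to these three homes and is open to secular trend, to home-by-cycle variation, and to changed detection of pain, since Intervention 1 trains staff in pain assessment itself.

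### Interrater agreement does not measure a before-after shift in assistants' pain ratings, and for the assistant-nurse difference it gives neither direction nor size

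*Protocol article*

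**What the plan says.** All of this is in the Methods of the protocol article.

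- **Targets.** The outcome list after Fig. 2 names "changes in the assessment of pain by healthcare worker on healthcare assistant level" as a tertiary outcome, followed by changes between the assistant and registered nurse groups. The matching hypotheses are introduced with "Furthermore the following hypotheses will be explored". One concerns assistants' assessment before and after the intervention. The other concerns a "difference in pain assessment between healthcare workers on assistant level and registered nurses level over time before and after the intervention".
- **Data.** "The documentation regarding the assessment of pain by nurses is always done in duplicate, by a health care worker on different education level". Ratings fall in three monitoring cycles, T0, T1 and T2.
- **Analysis.** After Fig. 3 the article says "A change in the assessment of pain by the healthcare workers is checked with interrater reliability tests", and then "By means of the interrater reliability test, a potential variation between the two nursing groups on assistant/secondary and tertiary level is monitored". It names no coefficient and does not say that coefficients are estimated per cycle and compared.
- **Other models.** The linear mixed models are assigned to pain intensity, duration and pain-free intervals. Staff level otherwise enters only where "event history analyses will focus on evaluating the influence of the two nursing professional groups" on pain events, which is not a test of change in assessment.

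**The concern.** The named method and the stated targets do not match. An interrater coefficient describes how closely two raters agree on the same resident. The first hypothesis asks whether one group's ratings moved over time, which is a different quantity. All healthcare workers in the intervention homes are trained, so a shift common to both staff levels is plausible, and an agreement coefficient is least informative in exactly that case.

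For the second hypothesis agreement is relevant, but a single coefficient hides whether assistants rate above or below nurses, and by how many points. Its value also depends on how variable and how common pain is among residents. The primary hypotheses expect 20% fewer pain events and 50% lower intensity, so a coefficient compared between cycles could move for reasons unrelated to rating skill.

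At stake is the interpretation of Intervention 1, which trains staff in pain assessment. These are the outcomes closest to that training.

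**Working it through.** The article gives no power, sample size or variance for the staff hypotheses, so there is no planned figure to reproduce. The stated 121 events and 179 persons belong to the Cox model and do not bear on this point. The variances and rater accuracies below are assumptions.

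**1. Common shift, one-sided shift, better precision.** Assume resident SD 1.5 (variance 2.25), rater error SD 1 (variance 1) and mean score 3. With two raters whose means differ by d, the rater variance component is d²/2.

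- ICC for absolute agreement = 2.25 / (2.25 + d²/2 + error variance).
- ICC for consistency = 2.25 / (2.25 + error variance).

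| Scenario | ICC agreement | ICC consistency |
|---|---|---|
| Baseline, d = 0 | 2.25/3.25 = 0.69 | 0.69 |
| Both groups 1 point lower, d = 0 | 2.25/3.25 = 0.69 | 0.69 |
| Assistants only, 1 point lower | 2.25/3.75 = 0.60 | 0.69 |
| Assistants only, 1 point higher | 2.25/3.75 = 0.60 | 0.69 |
| Error SD halved, d = 0 | 2.25/2.50 = 0.90 | 0.90 |

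A simulation of 200,000 rating pairs gave the same values. Kappa, with pain taken as a score of 2 or more, went from 0.47 to 0.49 under the common shift, a small movement that arises only because the shift changes how many scores pass the cut-off. That ICC is unchanged by an equal shift needs no variance assumption. The other values do.

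**2. Dependence of kappa on prevalence.** For two conditionally independent raters with sensitivity Se, specificity Sp and prevalence p, let q = p·Se + (1 − p)(1 − Sp). Then kappa = p(1 − p)(Se + Sp − 1)² / [q(1 − q)]. Take Se 0.80 and Sp 0.90, with the hypothesised 20% fall in pain events as a proxy for a fall in prevalence.

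- p = 0.20: q = 0.24; 0.0784/0.1824 = 0.430.
- p = 0.16: q = 0.212; 0.0659/0.1671 = 0.394.
- p = 0.80: q = 0.66; 0.0784/0.2244 = 0.349.
- p = 0.64: q = 0.548; 0.1129/0.2477 = 0.456.

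With Se = Sp = 0.85, kappa goes from 0.490 (p = 0.50) to 0.480 (p = 0.40). So with fixed raters kappa may fall, rise or hardly move. The Background cites pain in 19 to 83% of people with dementia, a range that reaches both ends.

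**3. Dependence of ICC on spread.** If resident variance falls from 1 to 0.25 with error variance fixed at 1, ICC goes from 1/2 = 0.50 to 0.25/1.25 = 0.20. If error variance falls in the same proportion, ICC is 0.25/0.50 = 0.50, with no change. The article does not say which applies.

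**4. What the duplicate ratings can identify.** Let m be residents' true mean pain in a cycle, and a and n the systematic rating tendencies of assistants and nurses. Mean ratings are m + a and m + n.

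- Change within assistants, T0 to T2: (m₂ − m₀) + (a₂ − a₀). This mixes true pain change with rating change.
- Staff level by cycle contrast: (a₂ − n₂) − (a₀ − n₀). True pain cancels because both rate the same occasion (assuming that rating tendencies are additive).

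This contrast is also zero under an equal shift. Such a shift appears only in the cycle effect, where these ratings alone cannot separate it from true pain change.

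**The case against.** The strongest reply is that agreement is a sensible target. Intervention 1 teaches correct use of one instrument, every assessment is documented by two staff levels, and coefficients per cycle could be compared. Halving rater error raises ICC from 0.69 to 0.90, so improved rating can be seen. This stands. A reader might infer that reliability tests cannot show change at all, or are the wrong statistic for both hypotheses; the documents do not support that. The article does not state the comparison between cycles, but a condensed article may leave it to the full protocol or analysis plan.

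A common shift would also not vanish from the trial. Pain intensity from the diaries is modelled across T0, T1 and T2 and would pick it up, though not separated from true pain change.

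It may also be said that naming a coefficient is a detail for the analysis plan. That is so, but the point does not rest on a missing detail. The article names a method for a stated target, and no choice of agreement coefficient turns it into a measure of the shift in assistants' ratings.

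Finally, the hypotheses are exploratory and the outcomes tertiary (the Background lists group differences as secondary). This limits the weight of the point but does not remove it.

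**Conclusion.** The point holds in a limited form. For the first staff hypothesis the planned statistic does not measure the target: ICC is 0.69 before and after an equal one-point shift, and the invariance is general. For the second, absolute agreement per cycle is relevant but incomplete: a one-point shift of assistants in either direction gives the same 0.60, and a consistency coefficient would miss it.

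Movement of ICC or kappa between cycles cannot be attributed to training alone, but its direction and size are not fixed by the documents. A reader might infer that the trial would report worsened agreement simply because pain fell. That does not follow: kappa falls from 0.43 to 0.39 at low prevalence and rises from 0.35 to 0.46 at high prevalence, and ICC need not move if error shrinks with pain. These figures rest on assumed accuracies and variances, and on pain events as a proxy for prevalence.

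A reader might also take the wording of the hypotheses, that a difference still exists, to mean that non-significance will be read as convergence. The article does not say so; it is only something to guard against. No primary conclusion is affected.

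**What to change.** Analyse the duplicate ratings with a linear mixed model: rating on staff level, cycle (T0, T1, T2) and their interaction, with random effects for resident and jointly rated occasion, and for rater where raters are identified. Account for home.

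- Make the paired staff-level by cycle contrast the main result. Give the assistant-minus-nurse mean difference with its confidence interval in each cycle, and the change between cycles.
- Report the cycle effect within assistants for the first hypothesis, and state that it mixes true change in pain with change in rating behaviour.
- Keep ICC (absolute agreement) or kappa per cycle, with confidence intervals, as a descriptive complement, and show the spread and prevalence of pain beside it.
- State that a non-significant difference will not be read as agreement.

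The cost is a change of analysis wording and one extra model. The duplicate ratings are already planned, so no new data are needed.
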